### Blinding

Outcome evaluators of pre- and postintervention measurements will be blinded to the group allocation (single blinding). To ensure blinding and blind-keeping of outcome assessors, detailed study-specific guidelines for all relevant procedures related to blinding and blind-keeping of outcome assessors have been established, which will be followed by all involved study investigators. For data assessed throughout the intervention period (ie, only applicable to the intervention group), blinding of investigators is not possible. The blinding of participants will also not be possible because usual care will be used as a control intervention.

### Participant Retention

Once a patient is included, a trained investigator will be assigned as the person responsible for supervision and correspondence with the respective study participant and will make all reasonable efforts to achieve participant’s retention in the study. Examples include providing written information sheets and reminders about study appointments, involving carers or relatives as personal support for study participants, and providing assistance with travel to the study center. Specifically, in the intervention group, each participant is provided with a training manual that is individually adapted to ensure that they use the training system correctly.

### Data Management

All study investigators will be thoroughly trained for all study procedures according to the Guidelines of Good Clinical Practice and in line with detailed working instructions and a data management plan (Multimedia Appendix 1). In short, local principal investigators are in charge for methodological standards and quality of data collection using data management system Castor EDC (Ciwit BV) [201]. The data management plan specifies standard procedures for data management, evaluation, and storage. All data entries will be cross-checked by a second investigator before exporting for analysis. Range checks for data values were preprogrammed for data entry into the eCRFs. To minimize bias during the assessment of all clinical outcome measures, detailed working instructions were prepared, including standardized measurement procedures and standardized instructions of participants for all measurements.

### Statistical Methods

Statistical analysis will be executed using R (The R Foundation), in line with RStudio (RStudio Inc). For demographics as well as training adherence and compliance, all collected data will be included (ie, including data of dropouts up to the time point of their withdrawal). For primary and all secondary outcomes, the data of all participants who completed pre- and postintervention measurements, regardless of protocol adherence, will be included in the statistical analyses. Questionnaire scores will be regarded as ordinal data. Data will be reported as mean (SD) values for continuous parametric data and median (IQR) values for continuous nonparametric data.

For all outcomes, descriptive statistics will be computed first. Normality distribution of data will be checked using the Shapiro-Wilk test. The level of significance will be set to *P*≤.05 (2-sided, uncorrected).

For all demographic variables, between-group differences (ie, intervention vs control) will be tested using an independent *t* test or Mann-Whitney *U* test in case the data are not normally distributed. For primary and secondary outcomes, the assumption of homogeneity of variance will be checked using Levene test. In case all assumptions for a 2-way analysis of covariance (ANCOVA) are met, effectiveness of the “Brain-IT” training will be analyzed using a two-way ANCOVA with the premeasurement value as covariate for the predicting group factor and the postmeasurement value as outcome variable [202]. If not all assumptions are met, the Quade nonparametric ANCOVA will be used. Because of the stratification by sex in the randomization process, no sex-specific statistical analysis will be computed. However, if there are relevant between-group differences in sex distribution or other demographic variables, these will be included in the statistical analyses as additional covariates. To determine whether the effects are substantive, partial eta-squared (η^2^_p_) effect sizes will be calculated for all primary and secondary outcomes. Effect sizes will be interpreted as small (0.01≤η^2^_p_<0.06), medium (0.06≤η^2^_p_<0.14), or large (η^2^_p_>0.14) [203].

Statistical analysis will be performed by PM after data collection is completed. As this is a small-scale RCT, no interim analysis will be performed.

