### Objectives and Hypotheses

This study explores the effectiveness of the “Brain-IT” training in improving global cognitive functioning in older adults with mNCD. With this, we aim to obtain a sufficiently precise estimate of the treatment effect to minimize the sample size needed for a future full-scale RCT.

Null Hypothesis (H_0_0): In older adults with mNCD, the addition of the “Brain-IT” training to usual care has no significant effect on global cognitive functioning compared with usual care.Alternative Hypothesis (H_A_): In older adults with mNCD, the addition of the “Brain-IT” training to usual care results in differing effects on global cognitive functioning compared with usual care.

As secondary objectives, the effects of the “Brain-IT” training on (a) domain-specific cognitive functioning (ie, learning and memory, complex attention, executive function, and visuospatial skills), (b) brain structure and function, (c) spatiotemporal parameters of gait, (d) instrumental activities of daily living (IADL), and (e) psychosocial factors (ie, QoL [quality of life], and levels of depression, anxiety, and stress), and (f) cardiac vagal modulation (ie, resting vagally-mediated heart rate variability [vm-HRV]) in older adults with mNCD as compared with usual care will be explored. (B) Brain structure and function will be evaluated to explore the possible underlying neural changes in training in relation to adaptations in cognitive performance. The following hypotheses are formulated for the remaining outcomes:

Null Hypothesis (H_0_): In older adults with mNCD, the addition of the ‘Brain-IT’ training to usual care has no significant effect on (a) domain-specific cognitive functioning, (c) spatiotemporal parameters of gait, (d) IADL and (e) psychosocial factors (ie, QoL, and levels of depression, anxiety, stress), and (f) cardiac vagal modulation (resting vm-HRV) compared with usual care.Alternative Hypothesis (H_A_): In older adults with mNCD, the addition the “Brain-IT” training to usual care results in differing effects on (a) domain-specific cognitive functioning, (c) spatiotemporal parameters of gait, (d) IADL, (e) psychosocial factors (ie, QoL, and levels of depression, anxiety, and stress), and (f) cardiac vagal modulation (resting vm-HRV) compared with usual care.

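### Assumption pretests on the trial data choose the primary analysis between ANCOVA and a rank ANCOVA, and what is pretested is left open

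*Protocol article*

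**What the plan says.** Protocol article, Statistical Methods, sets a decision rule for every primary and secondary outcome:

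- Normality: "Normality distribution of data will be checked using the Shapiro-Wilk test". The variable tested (pre value, post value or model residual) and the grouping (by arm or pooled) are not given.
- Variance: "the assumption of homogeneity of variance will be checked using Levene test".
- Level: "The level of significance will be set to *P*≤.05 (2-sided, uncorrected"). No other level is given for the pretests.
- Branch 1: "In case all assumptions for a 2-way analysis of covariance (ANCOVA) are met", the post value is analysed by group with the pre value as covariate.
- Branch 2: "If not all assumptions are met, the Quade nonparametric ANCOVA will be used".
- Effect measure: partial eta-squared; the "effect sizes will be calculated for all primary and secondary outcomes". No adjusted mean difference or confidence interval is named in either branch.
- Descriptives: mean (SD) for parametric data, but "median (IQR) values for continuous nonparametric data".

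The Methods paragraph of the Abstract repeats the either/or. Objectives and Hypotheses gives the purpose: "we aim to obtain a sufficiently precise estimate of the treatment effect", so that a full-scale trial can be sized. The Primary Outcome section takes a change of 3 or more Qmci points as clinically meaningful. The Sample Size section plans the future trial with the same primary outcome and an SMD of 0.5.

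**The concern.** ANCOVA compares baseline-adjusted means. Quade's method ranks both variables, regresses the post ranks on the pre ranks, and compares the residuals between arms. The two answer different questions, so a rule that chooses between them after seeing the data leaves the primary estimand open until then.

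The pretest is also a poor guide. It fires by chance at a fixed rate whatever the sample size. It may fire on a feature that ANCOVA does not assume, such as the shape of the baseline distribution. With arms this small it often misses real skewness.

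What is at stake is the estimate more than the test. The trial's result is meant to inform the size of the next one. In the Quade branch the planned output is a rank-based P value and a partial eta-squared computed on ranks, possibly beside medians and IQRs. None of these is a Qmci difference or an SD.

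**Working it through.** **Inputs from the article.** Two-sided 5% level; Shapiro-Wilk and Levene pretests; SMD 0.5; 14 per arm before attrition; recruitment of 17 to 20 per arm (14 × 1.2 = 16.8 and 14 × 1.4 = 19.6). With 17 recruited and the anticipated 20% attrition, 17 × 0.8 = 13.6 would be analysed, so 14 to 20 per arm is the relevant range.

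**Assumptions.** Pre-post correlation 0.5 or 0.7 (the article gives none); pretests at 5%; bivariate normal data with equal variances and parallel slopes, so ANCOVA is exactly right.

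**The plan's own figure.** The article gives no switching probability to reproduce. Its 14 per arm can be reproduced by minimising pilot plus main-trial size with the variance inflated to its 80% upper confidence limit. Main n per arm = [26 / χ²(0.20; 26 df)] × 2 × (1.960 + 0.842)² / 0.5² = 82.4, so the total is 14 + 82.4 = 96.4, the minimum. The article does not say which variant was used.

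**Step 1, analytic check.** Two independent 5% pretests give at least one false alarm with probability 1 − 0.95² = 0.0975. Three give 0.143 and five give 0.226.

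**Step 2, simulated switching rate** (5,000 trials per setting; 14, 17 and 20 per arm; both correlations; SMD 0 and 0.5):

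| Reading of the rule | Switch to Quade |
|---|---|
| Shapiro-Wilk and Levene once each, on ANCOVA residuals | 8 to 10% |
| The same, plus a slope-homogeneity test | 13 to 14% |
| Post values by arm, plus Levene | 12 to 14% |
| Pre and post values by arm, plus Levene | 20 to 22% |
| The same, plus a slope-homogeneity test | 23 to 25% |

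The rate does not fall as n rises, because these are false alarms at a fixed level. If baseline Qmci were spread evenly over the 45 to 62 entry window of the screened-MCI route (a further assumption; 17 per arm, correlation 0.7), the last reading gives about 40%. The residual-based reading stays at about 8%.

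**Step 3, protection given.** For data with skewness 1, Shapiro-Wilk rejects in about 20% of samples of 14 and 23 to 25% of samples of 17. For a pooled set of 28 to 40 values it rejects in about 41 to 58%.

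**Step 4, consequences under normality.**

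- Type I error, averaged over the six null settings: 0.051 for ANCOVA alone. For the two-stage rule it is 0.052, on both the narrowest and the broadest reading.
- Power at SMD 0.5 and correlation 0.7, at 14, 17 and 20 per arm: ANCOVA 0.42, 0.49 and 0.57; Quade 0.38, 0.45 and 0.52. The loss is about 4 to 5 points. At correlation 0.5 it is 2 to 3 points.
- The two tests disagree on significance in about 9 to 12% of trials.
- Partial eta-squared falls in a different class of the article's scale (including below small) in about 23 to 29% of trials. At correlation 0.7 its median is about 0.10 on ranks against 0.12 from ANCOVA.

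**Step 5, what ANCOVA would deliver.** The half-width of the 95% CI for the adjusted difference is about t(0.975; 2n − 3) × √(1 − r²) × √(2/n) in SD units. For n = 14 and r = 0.7 this is 2.060 × 0.714 × 0.378 = 0.56. For 17 and 20 per arm it is 0.50 and 0.46.

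**The case against.** A reader might infer that a chance pretest result destroys the Qmci-point estimate the trial was set up to produce. The documents do not support that. The article speaks of an estimate of the treatment effect, never of one in Qmci points, and the only effect measure it names is partial eta-squared, which can be computed on ranks. Nothing forbids reporting an adjusted mean difference beside a Quade P value, and the anonymized data are to be deposited, so the difference stays computable. Partial eta-squared from ANCOVA would itself need the pre-post correlation before it could be turned into an unadjusted SMD, so that difficulty does not come from the switch. All of this stands. What remains is that the planned analysis in the Quade branch does not itself supply the difference.

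A reader might also take a switching rate above 20% as the figure. It belongs to the broad readings, which test the baseline values. ANCOVA does not assume a normal covariate, and the wording leaves residual testing possible. The figure is a range that starts near 8%.

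Nor is this an error-rate problem. The fallback is a single method named in advance, type I error holds, and the Limitations section already expects low power and calls for confirmatory studies.

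An unseen analysis plan could add a mean difference or specify the pretests. It would still have to override a rule that the article states outright for the primary outcome.

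**Conclusion.** The point holds as one of pre-specification. The primary analysis is selected by pretests on the trial data, and the object of those tests is not fixed. With all ANCOVA assumptions true, the chance of switching is about 8 to 10% if residuals are tested and about 20 to 25% if pre and post values are tested by arm. These figures assume 5% pretests, normal data and a pre-post correlation of 0.5 or 0.7. Type I error is not materially affected. The harm lies in the estimand and its interpretation: about 9 to 12% disagreement on significance at SMD 0.5, a power loss for Quade of about 2 to 5 points depending on the correlation, and a branch with no planned baseline-adjusted Qmci difference and possibly no mean and SD. That such a difference is what planning needs is inferred from the stated objective, the 3-point threshold and the SMD-based sample size. The article does not say so itself. The change is worth making because it is cheap and serves the stated aim; the rule does not invalidate the trial.

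**What to change.** Before outcomes are analysed by group, state that the primary analysis of Qmci is the ANCOVA of the post score on group with the pre score as covariate, whatever any assumption test shows. Report the adjusted mean difference in Qmci points with its 95% CI, and the mean and SD by arm at both time points, even if the data look skewed. Name one robust option in advance, for example HC3 standard errors, and use it for both the interval and the P value, so that no second choice is left open. Check residuals graphically, and report Quade only as a sensitivity analysis.

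This takes the chance of a pretest-driven switch to zero. It costs a few sentences and a few lines of R. The downside is a slight loss of efficiency if the residuals turn out strongly skewed.

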### Trial Design and Study Setting

A 2-arm, prospective, parallel-group, single-blinded (ie, outcome evaluator of pre- and postintervention measurements blinded to group allocation) RCT with a 1:1 allocation ratio (ie, intervention: control), including 34 to 40 older adults with mNCD, will be conducted between May 2022 and December 2023. The control group will proceed with usual care as provided by the (memory) clinics where the patients are recruited, while the intervention group will perform a 12-week training intervention according to the “Brain-IT” training concept in addition to usual care (see section “Methods—Interventions”). The study was registered at clinicaltrials.gov before the start of patient recruitment (NCT05387057; date of registration: May 18, 2022; see Table 1 for details) and will be reported according to “The Consolidated Standards of Reporting Trials (CONSORT) 2010 statement” [93] and elaboration paper [94]. The study setup is multicentric (Zurich and St. Gallen) and national (Switzerland).

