DTI data will be processed using the TractoFlow pipeline [152,153], a diffusion MRI tractography processing pipeline based on Nextflow [154] and Singularity [155], for human brain tractography reconstruction. In patients with m-MNCD, DTI abnormalities are concentrated in the posterior regions, whereas the most reported regions of DTI alterations are the temporal lobes, with a particular emphasis on the parahippocampal white matter and posterior cingulum [156,157]. Therefore, MD and FA will be calculated for the parahippocampal white matter and posterior cingulum, defined as key ROIs for this study. In addition, tract-based spatial statistical analysis will be performed to study white matter changes at voxel-to-voxel (whole-brain) levels. Tract-based spatial statistical analysis is based on a general linear model and will be performed using FSL’s randomization tool [158] with 5000 permutations to correct for multiple comparisons (*P*<.05, corrected). All results will include threshold-free cluster enhancement [159]. The threshold-free cluster enhancement correction method is somewhat similar to cluster-based thresholding but is generally more robust and avoids the need for an arbitrary initial cluster-forming threshold. Two contrasts will be computed at the individual and group levels, testing for positive and negative differences in FA and MD parameters pre- and postintervention. We will include age and sex as key covariates in the general linear model.

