### Randomization

#### Sequence Generation

Participants will be randomly allocated to the intervention or control group. Variable block randomization (ie, block sizes=4, 6, and 8) with a 1:1 allocation ratio stratified by sex and institute (study center) will be used.

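### Randomisation is stratified by sex and centre, but the stated ANCOVA contains neither, and other covariates enter only if the arms are seen to differ

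*Protocol article*

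**What the plan says.** Under Randomization, Sequence Generation, variable block randomisation "with a 1:1 allocation ratio stratified by sex and institute (study center) will be used". The trial has two centres, Zurich and St. Gallen (Trial Design and Study Setting), so there are four sex-by-centre strata.

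Statistical Methods gives the model for the primary and secondary outcomes as a "two-way ANCOVA with the premeasurement value as covariate for the predicting group factor and the postmeasurement value as outcome variable". A Quade nonparametric ANCOVA replaces it if assumptions fail. Centre is not mentioned anywhere in that section. On sex it says "Because of the stratification by sex in the randomization process, no sex-specific statistical analysis will be computed". The next sentence adds that "if there are relevant between-group differences in sex distribution or other demographic variables, these will be included" as additional covariates. Demographics are compared between arms with a t test or Mann-Whitney U test.

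Interventions, Control Group contains a second rule of the same kind: relevant between-group differences in usual care will be accounted for in the analysis. Neither rule has a threshold.

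**The concern.** Two things are at stake.

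**The model depends on the data.** Which covariates the primary analysis contains is settled only after the arms have been compared, by a criterion that is not written down. More than one primary result is then compatible with the plan. In a randomised trial, differences in baseline characteristics arise by chance, and their observed size is a poor guide to whether a covariate will improve the estimate.

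**The analysis does not follow the design.** Stratified allocation keeps sex and centre balanced between arms, which makes the effect estimate less variable if those factors are prognostic. A model without them leaves their variance in the error term and gives no credit for that gain. The nominal standard error is then larger than the true one, and confidence intervals are wider than they need be. This trial's stated purpose is a sufficiently precise effect estimate for a future full-scale RCT, and its Limitations section expects insufficient power. It should not give up precision that its own design has already bought.

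**Working it through.** **Sample sizes.** Sample Size gives 14 per arm, raised for 20% to 40% attrition. 14 × 1.2 = 16.8, rounded to 17, and 14 × 1.4 = 19.6, rounded to 20. This reproduces the stated 17 to 20 per group (34 to 40 in total). The check uses N = 28 (2 × 14), 34 and 40, SMD 0.5 and two-sided 5%, all from the article.

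**Assumed inputs.** The documents do not give the pre-post correlation or the effects of sex and centre. Assumed: correlation 0.7, and an effect of d SD for each of sex and centre on the post score beyond the pre value.

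**Approximate size by formula.** With outcome SD 1, the residual variance given the pre value is 1 − 0.7² = 0.51. A factor split evenly in two with effect d contributes d²/4, so two factors contribute d²/2. Ignoring degrees of freedom,

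SE ratio (without / with the factors) ≈ √[(0.51 + d²/2) / 0.51].

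- d = 0: 1.00
- d = 0.2: √(0.53/0.51) = 1.02
- d = 0.5: √(0.635/0.51) = 1.12

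**Simulation.** 4000 runs per cell, four strata, permuted blocks of 4, 6 and 8, ANCOVA on the pre value without and with sex and centre:

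| d | N | SE ratio | Type I error, without / with | Power, without / with |
|---|---|---|---|---|
| 0 | 34 | 0.995 | 4.2% / 4.3% | 49.3% / 48.4% |
| 0 | 40 | 0.996 | 4.8% / 4.6% | 57.4% / 57.1% |
| 0.2 | 28 | 1.013 | 4.7% / 5.1% | 38.8% / 39.4% |
| 0.2 | 34 | 1.015 | 5.0% / 5.2% | 47.0% / 47.7% |
| 0.2 | 40 | 1.017 | 4.2% / 4.8% | 55.3% / 56.4% |
| 0.5 | 28 | 1.11 | 3.3% / 5.6% | 34.8% / 41.4% |
| 0.5 | 34 | 1.113 | 3.0% / 4.4% | 42.1% / 50.3% |
| 0.5 | 40 | 1.113 | 3.1% / 4.8% | 47.8% / 56.4% |

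At d = 0 and N = 28 the SE ratio is 0.993. The Monte Carlo error is about 0.3 points for a 5% rate, √(0.05 × 0.95/4000), and about 0.8 points for power near 50%, √(0.25/4000). The power loss at d = 0.5 is 7 to 9 points. At d = 0.2 or below it is lost in the noise.

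**If the factors shift pre and post equally.** A shift of 0.5 SD in both scores leaves only about (1 − 0.7) × 0.5 = 0.15 SD unexplained by the pre value. Simulated with shifts of 0.3 to 0.5 SD, the SE ratio is 0.996 to 0.999 (N = 28), 0.998 to 1.004 (N = 34) and 1.000 to 1.005 (N = 40). With shifts of 0.5 SD, power without and with the factors is 40.6% and 40.8%, 49.4% and 49.6%, and 55.6% and 55.6%. Type I error over these runs is 4.5% to 5.7% without the factors and 4.5% to 5.4% with them. There is no loss.

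**Whether the conditional rule repairs the omission.** Stratification keeps sex balanced, so the rule will seldom bring sex in. With an assumed trigger of a 15-point imbalance, sex enters in about 1% to 5% of simulated trials, and standard error and power stay as in the model without it. Centre is not named as a candidate.

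**How often some other covariate would enter.** The article does not define relevant. If it meant P ≤ .05, the chance that at least one of k independent demographics triggers is 1 − 0.95^k: 19% for k = 4, 26% for k = 6 and 34% for k = 8.

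**The case against.** The strongest reply concerns size. A reader might infer that the planned standard errors are too wide and the primary P value miscalibrated as a matter of course. The documents do not support that. A stable difference between the sexes or between sites would mostly show in both measurements, and the planned model already adjusts for the pre value. The loss appears only if sex or centre predicts the post score beyond the pre value, and nothing in the article says that they do. This objection stands, so the precision part is stated as conditional, with a range that starts at nil.

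Second, a reader might infer bias or a raised false-positive rate from omitting the strata. Neither follows: omitting balanced factors does not bias the estimate, and any resulting error is conservative. The trial also calls itself exploratory and expects confirmatory studies. This stands, and it limits the severity.

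Third, the sentence on sex may mean only that there will be no subgroup analysis by sex. That is a fair reading. The point does not depend on it, because the following sentence makes sex as a covariate conditional on observed imbalance.

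Fourth, the imbalance rule is at least written in advance, the baseline tests are not expressly tied to it, and a threshold could stand in an analysis plan that is not shown. It is true that the article does not link relevance to a P value, so the 19% to 34% above is illustrative. But the article states the model and the rule outright. The criticism is of what is stated: a threshold would make the rule reproducible, but covariate choice would still depend on observed imbalance.

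**Conclusion.** The point holds in two parts. The first needs no assumption: the covariates of the primary model depend on observed between-group differences under an undefined criterion, and the stratification factors are not in the stated model. The second is conditional: with effects of sex and centre of 0 to 0.5 SD each beyond the pre value and a pre-post correlation of 0.7, the planned standard error is 0.99 to 1.12 times the adjusted one, and power at SMD 0.5 falls by 0 to 10 points. With equal shifts in pre and post there is no loss. The prognostic strength and the correlation are assumptions. The sample size of 34 to 40 is unaffected. This should be fixed because the improvement is nearly free, but it does not threaten the validity of the treatment comparison.

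**What to change.** - State the model for the primary outcome and for the secondary outcomes analysed by ANCOVA as: post value = group + pre value + sex + centre, with sex and centre as fixed effects.
- Carry the same covariates into the Quade fallback and say so.
- Delete the imbalance-triggered covariate rules from the primary analysis, in Statistical Methods (demographics) and in Interventions, Control Group (usual care).
- Name any further covariate now, and use it whatever its observed balance.
- Describe baseline characteristics by arm, and do not test them to select covariates.

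The cost is wording and two degrees of freedom. If neither factor matters, power at N = 34 goes from 49.3% to 48.4%, about one point. Sex and centre are already recorded for the randomisation.

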To the best of our knowledge, the smallest unit of clinically meaningful change has not yet been determined for the Qmci. However, changes in Qmci scores were very similar to changes in standardized ADAS-cog scores. Longitudinal data of more than 360 patients with m-MNCD were analyzed for responsiveness of the Qmci and the standardized ADAS-cog [125] by calculating standardized response mean from baseline to scores obtained at 1, 3, 6, 9, and 12 months. The mean change between months 1 and 12 was 5 points (SD 7.56) for the standardized ADAS-cog scores, and 5.41 points (SD 10.02) for the Qmci. The paired-samples *t* test showed no statistically significant difference in standardized response means for standardized ADAS-cog and Qmci (t_357_=0.32; *P*=.75) [119]. Therefore, it is anticipated that the smallest units of clinically meaningful changes between these 2 measures are similar. For the standardized ADAS-cog, the minimal clinically relevant change is estimated to be 3 points for individuals with mNCD compared with ≥4 points based on previous recommendations made by a consensus committee of the Food and Drug Administration for patients in more advanced stages [126,127]. Therefore, it is assumed that a change of ≥3 points in the Qmci score can be regarded as a clinically meaningful change.

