### Sample Size

The optimal sample size was justified based on Whitehead et al [193], and the following assumptions: the future main (full-scale) RCT will be planned with identical design and primary outcome as this study, with a two-sided type 1 error rate of 5% and a statistical power of 80%.

Our pilot feasibility RCT revealed a medium effect size (η^2^_p_=0.080; under peer review; registered at ClinicalTrials.gov NCT04996654). The observed medium effect size is slightly higher than the pooled evidence of exergame-based or combined motor-cognitive training interventions in older adults with NCD on global cognitive functioning. For exergame-based interventions in individuals with mNCD, Wang et al [194] reported a medium SMD of 0.57 (*P*=.21, 95% CI −0.32 to 1.47; *k*=1; n=20, compared with cognitively active control), while Gavelin et al (2021) reported an SMD of 0.13 (*P*>.05, 95% CI −0.22 to 0.48; *k*=2; n=109, compared with passive control) [63]. Stanmore et al [195] reported a small pooled effect of Hedges *g*=0.340 (*P*=.02, 95% CI 0.06-0.62; *k*=6; n=193) for patients with cognitive impairment. Further meta-analytic results for individuals with mNCD are limited to simultaneous motor-cognitive training with reported small-to-medium effect sizes, including SMDs of 0.45 [61], 0.48 [196], 0.531 [61], and 0.69 [197]. On the basis of this, a medium effect size of a SMD of 0.5 seems reasonable and is anticipated. This leads to a justified optimal sample size of n=14 per arm.

In our pilot feasibility RCT, we observed an attrition rate of 20% (under peer review, registered at ClinicalTrials.gov NCT04996654). This is consistent with recent systematic reviews synthesizing mean attrition rates of 17% (range, 0 to 59%) [198] in physical training interventions, 10% for combined motor-cognitive training interventions [199], and 15% (range 0%-31%) [200] for exergame-based interventions for patients with m-MNCD. Therefore, an attrition rate of 20% is anticipated. To ensure an adequate number of participants, a wide upper safety margin for an attrition rate of up to 40% is selected.

On the basis of these considerations, we will aim to recruit 17 to 20 older adults with mNCD per group, leading to a total sample size of 34 to 40. This will provide a sufficiently precise estimate of the treatment effect to minimize the sample size needed for a future full-scale RCT [193].

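### Partial eta-squared bands are the stated test of whether effects are substantive, but they carry no sign and are often reached by chance at this sample size

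*Protocol article*

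**What the plan says.** Statistical Methods specifies a "two-way ANCOVA with the premeasurement value as covariate for the predicting group factor and the postmeasurement value as outcome variable", with the Quade nonparametric ANCOVA as fallback when assumptions fail. The analysis set is complete cases: "the data of all participants who completed pre- and postintervention measurements, regardless of protocol adherence, will be included in the statistical analyses". Significance is set at P≤.05 ("2-sided, uncorrected").

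The section then gives the effect size its purpose: "To determine whether the effects are substantive, partial eta-squared" values will be computed for all primary and secondary outcomes. They are read as follows: "Effect sizes will be interpreted as small (0.01≤η^2^_p_<0.06), medium (0.06≤η^2^_p_<0.14), or large (η^2^_p_>0.14"). The Methods paragraph of the Abstract states the same purpose. Neither place says which band makes an effect substantive.

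Three other places bear on this:

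- Primary Outcome adopts a benchmark in score units: 3 or more "points in the Qmci score can be regarded as a clinically meaningful change". It is set by analogy with the standardized ADAS-cog.
- Table 2 lists, for each outcome, which direction is improvement.
- Objectives and Hypotheses, and Sample Size, say the trial is meant to estimate the treatment effect precisely enough to plan a full-scale trial.

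**The concern.** Partial eta-squared is the share of outcome variance assigned to group after adjustment for baseline. As the criterion for a substantive effect it has three weaknesses here.

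1. It has no sign. A decline and an equally large gain earn the same label.
2. In a trial this small, sampling error alone usually produces a value above 0.01 and not rarely one above 0.06.
3. It is not in Qmci points, so it cannot be compared with the 3-point benchmark, and it is not the treatment-effect estimate the trial says it is for.

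At stake is how the primary result and a long list of uncorrected secondary outcomes are described, and what is carried into the decision on a full-scale trial. Because no cut is named, the choice of band is also left open until the data are known.

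**Working it through.** **Numbers analysed.** Sample Size gives 14 per arm before attrition, so 28. That figure can be reproduced. Take main-trial n per arm = 2(z₀.₉₇₅+z₀.₈₀)²/0.5², inflate it by the 80% upper confidence limit of the pilot variance, and minimise the total of both trials; the minimum is at 14 per arm. The recruitment range follows from 14×1.2 = 16.8 → 17 and 14×1.4 = 19.6 → 20 per arm, so 34 to 40 in total. I use N = 28, 34 and 40. The last two assume no losses. At the anticipated 20% attrition, 0.8×34 = 27.2 and 0.8×40 = 32 would be analysed.

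**Distribution with no true effect.** The model has one group degree of freedom and one covariate, so error df = N − 3. Partial eta-squared = SS_group/(SS_group + SS_error) = F/(F + df). With no group effect it follows Beta(1/2, df/2), with mean 1/(1 + df) = 1/(N − 2).

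Worked case, N = 28, df = 25:

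- Mean = 1/26 = 0.038.
- A value of 0.06 corresponds to F = (0.06/0.94)×25 = 1.60, with P = 0.218.
- For P = .05, eta-squared must be t²/(t² + 25) with t = 2.06, which is 0.145.

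| N analysed | df | Null mean | P(≥0.01) | P(≥0.06) | P(≥0.14) | Value needed for P=.05 |
|---|---|---|---|---|---|---|
| 28 | 25 | 0.038 | 0.62 | 0.22 | 0.055 | 0.145 |
| 34 | 31 | 0.031 | 0.58 | 0.17 | 0.032 | 0.118 |
| 40 | 37 | 0.026 | 0.55 | 0.13 | 0.019 | 0.100 |

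Simulating 20,000 ANCOVAs at each N gave 0.618, 0.582 and 0.546 for the first band and 0.215, 0.171 and 0.133 for the second, in agreement. At N = 32 the two probabilities are 59% and 18%. If attrition reached the 40% margin (N about 20 to 24), they would be 65–68% and 26–31%.

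**Sign.** With no effect, the two directions are equally likely. At N = 28, a medium or larger label pointing towards harm has probability 0.218/2 = 0.109.

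**Across the secondary outcomes.** Table 2 lists 35 non-imaging secondary variables: 5 learning and memory, 4 attention, 5 executive, 2 visuospatial, 7 gait, 1 IADL, 4 psychosocial and 7 heart rate variability. If none were affected and N = 34, the expected number labelled small or more is 35×0.58 ≈ 20, and medium or more 35×0.169 ≈ 6. The expected number with P≤.05 is 35×0.05 = 1.75. These expectations hold whatever the correlation between outcomes.

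**Labels against points (illustration).** For equal groups, eta-squared = (d²/4)/(1 + d²/4). The protocol does not give the ANCOVA residual SD. The only Qmci change SD it cites is 10.02, for change between months 1 and 12 in another cohort. With that SD, 3 points is d = 3/10.02 = 0.299 and eta-squared = 0.0224/1.0224 = 0.022, labelled small. If the residual SD were half as large (5.01, an assumption), d = 0.599 and eta-squared = 0.0896/1.0896 = 0.082, labelled medium. The same 3 points takes a different label depending on the SD.

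**The case against.** The best defence is that the bands do not stand alone. The section names no band as the cut and sets a separate significance level. At N = 28, P≤.05 already requires about 0.145, which is in the large band, so false claims stay at 5% per outcome if label and test are read together. Table 2 gives directions and group summaries will be reported, so harm can be told from benefit. The protocol also presents the trial as exploratory and concedes under Limitations that it will probably be underpowered. All of this stands. It limits the consequence but leaves the stated criterion unchanged, because the criterion refers to none of these elements.

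Three stronger inferences are tempting, and the documents do not support them.

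- A reader might infer that the trial will declare some 20 null secondary outcomes substantive. That would require small to be the cut and the label to be read without its P value; the protocol says neither.
- A reader might infer that the analysis yields no difference in points and no confidence interval. This is a condensed article, the ANCOVA produces an adjusted difference, and such reporting is commonly left to the analysis plan. The fault is the criterion that is stated.
- A reader might infer that the pilot's 0.080, called medium under Sample Size, was only chance. The number analysed and the model behind it are not given. The planned effect also draws on several meta-analyses.

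**Conclusion.** The point holds as a badly chosen stated criterion, and it should be fixed. Partial eta-squared cannot separate benefit from harm. With 40 down to 28 analysed and no true effect, an outcome is labelled small or more with probability 55–62%, and medium or more with probability 13–22%. Small is thus the usual chance result, and medium a minority one of about 1 in 8 to 1 in 5. No planned test is made invalid; the problem is how size is judged.

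The figures assume the parametric ANCOVA with baseline as the only covariate and its usual normal-error conditions. Two further covariates would raise them slightly (N = 28: 63% and 24%). They are approximate for the Quade analysis and are not meant for the imaging outcomes.

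**What to change.** In the Abstract and in Statistical Methods, remove the use of eta-squared bands to decide whether effects are substantive, and state instead:

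- **Primary outcome:** the baseline-adjusted mean difference in Qmci score (intervention minus control) with its 95% confidence interval, read against the 3-point benchmark. Add that the benchmark was set by analogy with the ADAS-cog and as a change in score, so applying it to a between-group difference is a further assumption.
- **Secondary outcomes:** adjusted differences in natural units with 95% confidence intervals, labelled exploratory and read with the directions in Table 2.
- **Partial eta-squared:** retained, if wanted, as description only.

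**Cost:** for outcomes analysed by ANCOVA, the estimate and interval come from the same fit, so only wording changes. The Quade analysis gives no difference in points. Where it is used, a supplementary estimate is needed, for example the ANCOVA difference with a robust or bootstrap confidence interval. No extra data or participants are required.
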